### Emergency unblinding

Not applicable as serious adverse events are not known to occur in clinical practice.

### Data collection methods

Outcomes will be collected via self-reported questionnaires at baseline (i.e. prior to randomisation) and follow-up after six and 12 months. At six-month follow-up, participants will normally have completed their intervention (which normally extends between three to five months and should be started within 4 weeks of randomisation) and have been progressively implementing job accommodations and self-management at work. Data collection is via postal questionnaire with an on-line option available at six and 12 months, provided via e-mail with a weblink (using Research Electronic Data Capture (REDCap) [60]. The trial manager (baseline) and CTU (six and 12 months) will monitor return of questionnaires.

• **At 2 weeks** after questionnaire provision/mailing, if the questionnaire is not yet returned, the trial manager [baseline questionnaire] or CTU [six- or 12-month questionnaire] will text/e-mail/ telephone (as applicable) to remind the participant to return their questionnaire.

• **At 3 weeks** after questionnaire provision/mailing, if the questionnaire is not yet returned, the trial manager [baseline questionnaire] or CTU [six- or 12-month questionnaire] will mail a reminder letter and a further copy of the relevant questionnaire (with Freepost envelope).

• **If the six- or 12-month questionnaire are not returned by seven and 13 months, respectively,** the CTU will then telephone the participant to obtain a minimal data set. This will include at least the primary outcome measure (in the form of the WLQ-25 – WALS combined measure). The following key outcomes will also be collected if possible: job status (WTI part 1, if currently on sick leave, and date of stopping/changing job, if applicable; the WPAI, EQ-5D-5L; thereafter, the Work Transitions Index (WTI) parts 2,3 and 4, health resource use, work-related questions, and the SF-12. At 12 months, the RA-WIS will also be collected. If the CTU are unable to obtain this data, this will be recorded in the Trial Database and data entered as missing.

### Data management and confidentiality

#### Data validation

Data management personnel will validate each questionnaire prior to data entry, with self-evident errors corrected, and recorded. The trial manager or CTU trial administrators will contact the participant for clarification if required.

#### Data entry and coding

Data received as hard copy will be entered into the trial database by the CTU data entry personnel. Data entered online will be automatically entered into the trial database. For every 50 questionnaires entered, data entry will be verified by batch sampling a minimum of 10% of case report forms and verifying against the database entries. A record of errors will be recorded together with actions and resolutions. The type and number of errors found will inform the decision about increasing the verification scope and frequency, up to full data set verification. A Data Management Plan will be approved by the Trial Management Group (TMG) prior to implementation.

#### Confidentiality and data storage

Information about study participants will be kept confidential and managed according to the requirements of the Data Protection Act, NHS Caldicott Guardian, the Research Governance Framework for Health & Social Care, Ethics Committee Approval and University of Salford Research Governance Procedures. All study-related information will be stored securely at the University of Salford and Lancashire CTU. Data on central servers at either location is stored in password-protected restricted access folders only accessible to the relevant research teams at those sites. The REDCap secure web application for online questionnaire collection meets the requirements of internationally recognised International Council for Harmonisation of Technical Requirements for Pharmaceuticals for Human Use (ICH) Good Clinical Practice, Federal Drug Agency 21 Code of Federal Regulations Part 11 and the European Union Clinical Trials Directive. Data hosting storage exceeds International Organisation for Standardisation 27,001 Information Security Management requirements. All data collection, process, and administrative forms will be identified by a coded Patient Screening Number (PSN) or Participant Identification Number (PIN). Patient-identifiable data will be securely stored separately from data identified by PSN or PIN. Original baseline questionnaires, participant documents, treatment and interview audio-recordings and transcriptions will be securely stored at the University of Salford. Any hard copy six- and 12-month questionnaires will be stored at the Lancashire CTU until transferred to the University of Salford at the end of the study. Interview recordings will be deleted following transcription and analysis. Original data and records will be archived for 6 years at the Centre for Health Sciences Research, University of Salford.

#### Data transfer from the University of Salford to CTU

The trial manager at the University of Salford will ensure copies of all completed baseline questionnaires are provided, in a timely and secure manner (i.e. scanned and sent by e-mail using encrypted PDF), to the CTU for data entry.

#### Data access

The CTU Principal Clinical Trials Manager and Data Manager will oversee intra-study data sharing, with input from the Trial Statistician. To ensure confidentiality, data dispersed to the Supervising and Trial Statisticians, health economist, and contextual factors team will be blinded of any identifying participant information. Following analysis, the Chief Investigator will receive a copy of the final cleaned raw and final datasets and Stata code for the coding of data and analysis. The members of the Process Evaluation team will also have access to the pseudo-anonymised interview data, interview and treatment audio-recordings, WORKWELL WES-RCs and Treatment Record Forms.

### Statistical methods

Primary effectiveness analyses will follow a pre-specified Statistical Analysis Plan (approved by the Trial Steering Committee (TSC) and available on request) and will include the intention to treat population. Data will be summarised using means, medians or proportions as applicable. The primary analysis will use mixed effects linear regression to estimate the effect of group allocation on WLQ-25 summed index scores, controlling for the stratification variable in the randomisation process (skill level group) and the baseline value of the WLQ-25 (both fixed effects) and therapist (random effect); the six- month and 12-month outcomes will be analysed in a single model with an interaction term between time point (six or 12 months) and randomised group to determine the treatment effect at both time points separately. Secondary effectiveness analysis will repeat the primary analysis method for all other outcomes, using appropriate generalised linear mixed modelling methods (i.e. mixed effects linear, logistic or ordinal logistic regression) including six- and 12-month outcomes as available, controlling for the stratification variable, baseline value of the specific measure and therapist effect. The interaction between time point and randomised group will not be included for outcomes measured only at 12 months. Sensitivity analyses will include the analysis of the primary outcome measure excluding anyone allocated to the intervention who did not attend WORKWELL and anyone allocated to control but did receive WORKWELL (the per protocol population). We do not anticipate undertaking sensitivity analyses on the basis of missing data unless there is a great deal and/or large imbalance in missingness between the two trial groups.

We will also explore the effects of contextual effects on outcomes via sub-group analyses. This will be an exploratory analysis for hypothesis generation. Each sub-group analysis will be specified in advance of starting analysis, with a theoretical justification for its inclusion. Analysis will be based on tests of interaction between group and contextual factors, as part of regression models. Interpretation will not over-emphasise any statistical or non-statistical significance at the traditional 5% level given the likely lack of power, multiple sub-group investigations and expectation that any sub-group effects will not be substantial. The contextual factors analysis will be fully described in the Statistical Analysis Plan.

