**Contextual factors: environmental factors**					
Nature of work	Job skill level 1–4 (UK Standard Occupational Classification (SOC2010)) [48].	Main job title and industry working in	✓		
	Job responsibilities	e.g. overtime, variable hours; and need to travel for business	✓		
	Work demands	Two items: physical and mental work demands	✓		✓
	Control over work and flexibility [49]	Four items: control over work schedule, job flexibility, ability to postpone work tasks and help from colleagues with work	✓		✓
	Work productivity	One item: self-reported work productivity in the last 6 months	✓	✓	✓
Work Transitions	The Work Transitions Index (WTI)^a^ [43].	Includes a) employment status; b) 14 items assessing: job disruptions due to arthritis c) sickness absence due to arthritis or other conditions in the last 6 months; d) change in occupation or working hours in the last 6 months.	✓	✓	✓
Workplace Support	The Perceived Workplace Support Scale (PWSS) [50]	a 19-item questionnaire, of perceived managerial, co-worker and organisational support (REF)	✓		✓
	Work support services	Access to occupation health and work support services	✓		✓
Work Policies and Accommodations	The Workplace Accommodations, Benefits, Policies and Practices Scale (WABPPS) [51, 52]	17 items: job accommodations, policies and workplace practices available, use of and helpfulness	✓		✓
Organization Polices	Organization size	Numbers of employees in company	✓		

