**Contextual Factors: Personal**					
Personal appraisal	Job strain [53]	One item: stress currently experienced at work	✓		✓
	Work motivation/ importance/self-efficacy	3 items: motivation, importance and confidence to continue working (0–10 NRS) (0–10 NRS)			
	Disclosure [50]	Disclosure about condition to employer /line manager	✓		✓
	Job satisfaction	Satisfaction with job: 0–10 NRS	✓		✓
	Future job expectations	Two items: concerns about health affecting ability to work in future; and likelihood of leaving job in the next year due to arthritis	✓		✓
Work-Life Balance	Work-life balance [54].	Four items: perceived work-life balance taken from the Work, Health Life Balance Perceptions Scale	✓		✓

Notes: ^a^ the WLQ-25 and WALS will be collected within the Combined WLQ-25 WALS dual scored measure [41]

Each month, employment status and absenteeism will be collected by the Lancashire Clinical Trials Unit via e-mail or telephone

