### Data collection

The baseline questionnaire includes: demographic factors i.e. age, gender, living situation, ethnicity, educational qualifications; employment factors, i.e. employment status, main job title; hours worked, job features (e.g. working overtime, shift work), organisation size, work-related support services accessed; and condition specific factors, i.e. symptom duration, time since diagnosis. For each of the following outcomes, the metric will be the final value, and aggregated as means. The baseline, six- and 12-month follow-up questionnaires include (unless otherwise stated):

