#### Work- related outcome measures

i)The Work Limitations Questionnaire (WLQ-25): a 25-item reliable, valid measure of presenteeism, indicating the amount of time, in the last 2 weeks, a person was limited in: physical work demands, time demands, mental-interpersonal demands and output demands. The summed score (i.e. of the four sub-scales) will form the primary outcome measure [27].

Secondary outcomes include:
ii)**Presenteeism**:WLQ-25 sub-scales: the four subscales measuring physical work demands, time demands, mental interpersonal demands and output demands from specific items in the WLQ-25 questionnaire [27].The Work Activities Limitations Scale (WALS): a reliable, valid measure including 12 items assessing degree of difficulty performing work activities (0 = no difficulty; 3 = unable to do [40].

The WLQ-25 and WALS will be collected using the combined WLQ-25 and WALS, from which each can be calculated, as well as a dual-key scored outcome [41]. Subsequent to the trial starting, this dual-key scored outcome is now supported by the OMERACT Work Productivity Group as the current best available measure of presenteeism, and a better predictor of work cessation than the original WLQ-25 [41, 55].
The Work Productivity and Activity Impairment Questionnaire General Health V2.0 (WPAI:GH): a reliable, valid measure of extent of absenteeism, presenteeism, and impairment in daily activities attributable to general health [42].iii)Work status: whether in full- or part-time work at six and 12 months, collected using the Work Transitions Index [43];iv)Absenteeism**:** each month, the number of days sickness absence attributable to arthritis or other causes. This is collected by text, e-mail or telephone.v)RA-Work Instability Scale (RA-WIS): at 0 and 12 months: reliable, valid measure including 23 true/false items measuring mismatch between functional abilities and job demands [30]vi)Work Self-efficacy: at 0 and 12 months: three 0–10 numeric rating scales (NRS) asking about confidence in: ability to work; ability to manage their health condition at work; and working will not make their health worse. Additionally, three 0–10 NRS will be used to measure: motivation; importance and confidence to continue working over the next year.

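### Absenteeism is collected as days each month, but the stated metric and models cover only six- and 12-month values and have no denominator for time in work

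*Protocol article*

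**What the plan says.** Work-related outcome measures, item iv, makes absenteeism a secondary outcome of its own: "each month, the number of days sickness absence attributable to arthritis or other causes", collected by text, e-mail or telephone. The note under Table 1 adds that "Each month, employment status and absenteeism will be collected by the Lancashire Clinical Trials Unit via e-mail or telephone".

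The Data collection section introduces the list containing that item with "For each of the following outcomes, the metric will be the final value, and aggregated as means".

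Statistical methods then states that "Secondary effectiveness analysis will repeat the primary analysis method for all other outcomes". The models are to be fitted "using appropriate generalised linear mixed modelling methods (i.e. mixed effects linear, logistic or ordinal logistic regression) including six- and 12-month outcomes as available". Each of them is to be adjusted, "controlling for the stratification variable, baseline value of the specific measure and therapist effect". For outcomes with both time points, it separates the treatment effects at six and 12 months by an interaction with time.

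None of these places makes an exception for the monthly absence days. None states how the monthly reports are combined, what serves as their baseline value, or how months after leaving work are treated.

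**The concern.** A monthly count of days lost is usually skewed, with many zeros, and accrues only while a person is employed. The stated rules were written for questionnaire scores taken at two visits. Applied to this outcome they raise three problems.

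- **Information.** The month 6 and month 12 values are 2 of 12 reports.
- **Exposure.** The intervention aims at job retention, so months at risk of sick leave may differ by arm. The rules contain no denominator, though the monthly employment status would supply one.
- **Baseline.** The model requires a baseline value of the measure, but no monthly report before randomisation is described. The nearest baseline item is in the Work Transitions Index (Table 1), which asks about "sickness absence due to arthritis or other conditions in the last 6 months" and so has a different recall period.

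At stake is the precision, and possibly the direction, of a named secondary outcome. The primary outcome is unaffected.

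**Working it through.** **Inputs from the protocol.** There are 12 monthly reports over one year. Sample size gives 90 per arm with 12-month data, and 180 / 0.75 = 240 randomised reproduces its total. The protocol gives no figure for absence, so every rate below is an assumption.

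**Reports used.** Months 6 and 12 only: 2/12 used, 10/12 = 83% unused. Sums over months 1–6 and 7–12: none unused.

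**Precision with nobody leaving work.** Assume a control mean of 0.8 days per month, a true ratio of 0.6 (intervention mean 0.8 × 0.6 = 0.48), personal rates following a gamma distribution with shape 0.5, Poisson counts within person, no therapist effect and a two-sided 5% test. The variance of one person's mean over m months is μ/m + μ²/0.5. The difference is 0.80 − 0.48 = 0.32, its standard error is √[(v_control + v_intervention)/90], and power ≈ Φ(0.32/SE − 1.96).

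| Data used | v control | v intervention | SE | 0.32/SE | Power |
|---|---|---|---|---|---|
| Month 12 (m = 1) | 0.80 + 1.28 = 2.080 | 0.48 + 0.461 = 0.941 | 0.183 | 1.75 | 42% |
| Months 6 and 12 averaged (m = 2) | 0.40 + 1.28 = 1.680 | 0.24 + 0.461 = 0.701 | 0.163 | 1.97 | 50% |
| Months 7–12 (m = 6) | 0.133 + 1.28 = 1.413 | 0.08 + 0.461 = 0.541 | 0.147 | 2.17 | 58% |
| All 12 months (m = 12) | 0.067 + 1.28 = 1.347 | 0.04 + 0.461 = 0.501 | 0.143 | 2.23 | 61% |

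Simulations under these assumptions with 90 or 100 per arm gave 40% to 45% for month 12 alone and 65% to 70% for a negative binomial model of all months. Month 12 alone is the relevant comparator for the 12-month estimate, because the interaction with time separates the two effects.

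**Sensitivity.** A second simulation used 1 day per month, a ratio of 0.6, 90 per arm, added month-to-month variation, and between-person variance of 0.5, 1 and 2. Power was 25%, 19% and 15% for month 12; 42%, 34% and 24% for months 6 and 12; and 92%, 76% and 52% for all 12. With no true effect, the comparison of means rejected in 4.4% to 5.4% of trials.

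**When people leave work.** These simulations assume 0.8 days per month, shape 0.5, 90 per arm, and leaving more likely in people with high absence.

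- True ratio 0.6, leaving 10% control and 5% intervention: about 35% power for a raw sum of months 7–12 that gains nothing after leaving, against 63% for an all-months rate model.
- True ratio 1.0, leaving 20% and 10%, leavers set to missing at month 12: 13.8% false positives (600 trials; simulation SE √(0.138 × 0.862/600) = 1.4 points), against 5.3% for the rate model.
- If leaving is unrelated to absence, false positives stay at 5% to 7%.
- A linear model of days per month in work gives 61% to 64% power and 4% to 5% false positives.

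**The case against.** The strongest reply is that this is a condensed article. It cites a separate statistical analysis plan and asks for appropriate models, and variable derivation is ordinary content for that plan. The final value may mean the follow-up score rather than the change from baseline. Absenteeism is set apart as monthly, half-year sums would count as six- and 12-month outcomes without losing a report, and the WPAI-GH measures absence at exactly those visits. Much of this is fair. When nobody leaves, the half-year sum removes most of the loss (58% against 61% above). What stands is that the article does not merely omit a method. It states a metric and a closed model list and applies them to this outcome without exception. The half-year sum also still lacks a denominator.

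A linear model is not invalid here: it held its error rate in the simulations without leavers, and it does nearly as well as a count model once days are divided by months in work. Ordinal models can also accommodate many zeros. The weakness is the derivation more than the model family.

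A reader might infer that leavers would be credited with zero absence, so that the arm with better job retention looks worse. No section says so. The protocol is silent, it collects employment status monthly, and its nearest statement (Sample size, for the WLQ-25) counts people no longer working as non-completers. A reader might also infer that these days feed the employer-perspective economics. The Economic analysis section builds those scenarios on the WLQ-25, the WPAI and QALYs, and does not name monthly absence days.

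**Conclusion.** The point holds as a poor fit between how absenteeism is collected and how the protocol says it will be analysed. The main consequence is lost precision: about 45% power from month 12 alone against about 65% from all months, with an assumed mean of 0.8 days per month, a true ratio of 0.6 and nobody leaving. The gap widens if absence varies strongly from month to month, and nearly closes if the reports are summed by half-year and nobody leaves.

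Bias is conditional. It needs leaving work both to differ by arm and to be related to absence, and the protocol gives no figures from which to judge how likely that is. The baseline covariate for the monthly measure is also undefined. This is a secondary outcome and the trial's main conclusion does not depend on it, but the wording should be settled before analysis.

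**What to change.** Reconcile Data collection, Work-related outcome measures and Statistical methods on this outcome:

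1. Exempt absenteeism from the rule on final values aggregated as means.
2. Define it as total sickness-absence days over all monthly reports, per month reported and in employment.
3. Analyse it with a mixed negative binomial model with a log offset for those months, or a linear model of days per month in work, keeping the stratum and therapist terms.
4. Name the baseline covariate, for example the baseline six-month absence item of the Work Transitions Index.
5. State how months after leaving work are handled, and report work status alongside.

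The cost is wording in the analysis plan, since monthly absence and employment status are already collected. The drawback is that time in employment arises after randomisation and may be affected by treatment. The rate therefore describes absence while employed and should be read together with job retention.

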**Secondary outcome measures**					
Presenteeism	Work Activities Limitations Scale^a^ (WALS) [40]	12 items: degree of difficulty in work activities (0 = no difficulty; 3 = unable to do)	✓	✓	✓
	Combined WLQ-25 WALS^a^ [41]	Combination of above two measures	✓	✓	✓
	WLQ-25 [27]	4 subscales calculated from relevant items in the WLQ-25 questionnaire	✓	✓	✓
Absenteeism and Presenteeism	Work Productivity and Activity Impairment Questionnaire General Health V2.0 (WPAI-GH) [42]	Last 7 days: time off on sick leave/any other reason; hours worked; health problems effect on work productivity and ability to do other daily activities.	✓	✓	✓
Work status	Work Transitions Index [43]	Whether employed; in full- or part-time work	✓	✓	✓
Work instability	Work instability scale (RA-WIS) [30]	23 true/false items: degree mismatch between functional abilities and workplace demands	✓		✓
Work self-efficacy		0–10-point numeric rating scales (NRS) 0 = not at all to 10 = very. 3 work self-efficacy items (confidence in working, managing health condition at work and work not making condition worse (0–10 NRS)	✓		✓

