### Sample size

This was calculated using data from the feasibility study. The minimal clinically important difference for the WLQ-25 is estimated as 13 points in the summed score [57]. The standard deviation (SD), pooled across the intervention and control groups, was 20.64 in the feasibility trial. As the SD might be an under-estimate, the 80% upper one-sided confidence limit of the estimated SD, i.e. 23.02, was used. Although the WORKWELL trial is individually, rather than cluster randomised, we are concerned that the effect of the WORKWELL intervention may vary by therapist (as there is more than one therapist at 11 of the 22 hospitals in the 18 sites). This could lead to a clustering effect on outcome. No such effect is expected in the control intervention. We therefore performed the sample size calculation using the *clsampsi* Stata command [58]. As we do not expect the clustering effect to be large, the intra-class coefficient (ICC) for the WORKWELL intervention arm = 0.05 and control arm = 0. To identify a 13-point difference, SD = 23.02, *p* = 0.05 and 90% power, 90 participants are required in each group. Allowing for a 25% attrition rate at 12 months (i.e. non-completion of the WLQ-25 at 12 months due to no longer working or on long-term sick leave; or non-return of the 12-month questionnaire) we intend to recruit and randomise 240 participants in equal numbers to the two groups. We anticipate we may need to obtain consent from up to 300 patients to achieve 240 participants at randomisation (as some will not complete and return their baseline questionnaire, and some may become ineligible prior to randomisation) and 180 participants with 12-month outcome data.

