### Blinding

Due to the nature of the intervention it will not be possible for therapists to be blinded to group allocation. Therapists are informed not to provide the WORKWELL intervention to any other patients. None of the participating sites normally conduct full work assessments and detailed work provision. To reduce the risk of contamination of the control group (i.e. therapists providing control participants with JRVR), WORKWELL therapists will be informed which participants are in the control group. They will enter the participant’s details onto the Control Participant Log within the Trial Therapy site file. Therapists are requested to check with patients whether they are in the WORKWELL trial and check this Log before providing any brief work advice to patients. Participants cannot be blinded to the intervention they receive. However, we will present the study in the Participant Information Sheet as a trial comparing two methods of providing work advice, without any suggestion that one is preferable. The study explanation includes the conflicting evidence from previous trials and that full JRVR is rare in Rheumatology services. Thus, patients will be informed that, in either arm, they will receive more information about managing work problems than normally available. The trial manager and co-ordinating research team are not blinded to group allocation.

Data co-ordination and data entry staff at the CTU responsible for baseline and follow-up questionnaire management and contacting participants to obtain any missing data at follow-ups, will be blinded to group allocation. The CTU trial manager, data manager and information systems team will be unblinded. The Trial Statistician will initially conduct the analyses blinded to group allocation, ignoring the therapist clustering effects as these cannot be accounted for without knowing group allocation. After the results under blinding have been shared, the Trial Statistician will become unblinded and the analyses will be re-run accounting for therapist effects. Adjusting for therapist effects will only impact the precision of estimates, rather than their magnitude. The health economist will be not be blinded as the costs of WORKWELL will be included in the analysis.

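### For binary and ordinal outcomes the therapist effect changes the meaning of the odds ratio, not only its precision, and can move it away from 1 when risks are equal

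*Protocol article*

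**What the plan says.** The Statistical methods section analyses the WLQ-25 with a linear mixed model. Skill-level stratum and baseline are fixed effects, therapist is a random effect, and 6 and 12 months enter one model with a group-by-time interaction. The other outcomes follow the same method, "using appropriate generalised linear mixed modelling methods (i.e. mixed effects linear, logistic or ordinal logistic regression) including six- and 12-month outcomes as available", and "controlling for the stratification variable, baseline value of the specific measure and therapist effect". Work status is one of them. Table 1 lists it among the secondary outcomes as "Whether employed; in full- or part-time work", measured at both follow-ups.

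That section does not say in which arm the therapist effect applies. Two others bear on it. On therapist clustering, the Sample size section says "No such effect is expected in the control intervention" and sets "the intra-class coefficient (ICC) for the WORKWELL intervention arm = 0.05 and control arm = 0". The Blinding section has the statistician first analyse blind, "ignoring the therapist clustering effects as these cannot be accounted for without knowing group allocation", and re-run the analyses with therapist effects after unblinding. It then states: "Adjusting for therapist effects will only impact the precision of estimates, rather than their magnitude".

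**The concern.** With an identity link, a mean-zero random effect leaves the group coefficient as a difference in means, whichever arm carries the effect. The estimate may move a little because therapists are reweighted, but its target does not change.

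With a logit link it does. A coefficient conditional on a random effect is not the population-average coefficient, because odds ratios are not collapsible. If only WORKWELL participants carry a therapist effect, the WORKWELL log-odds describes an average therapist (random effect zero), while the control log-odds describes a whole population. The therapist-specific value lies further from zero, that is, further from a risk of 50%. For an outcome rarer than 50%, such as being out of work, equal risks then give an odds ratio below 1, which looks like better job retention on WORKWELL.

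Stacking 6 and 12 months can enlarge this. Someone out of work at 6 months is often still out at 12. Without a participant-level term, the therapist variance is the only place where the model can put that correlation.

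At stake is the estimate for the outcome that speaks most directly to keeping people in work. By the Blinding plan, the odds ratio could also move between the blinded and unblinded runs for a reason that the protocol rules out.

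**Working it through.** **Inputs.** ICC 0.05 for WORKWELL and 0 for control (Sample size; given for the WLQ-25, with none for a binary outcome). 240 randomised 1:1, so 120 per arm. Therapists: 11 of 22 hospitals have more than one, so at least 11 × 1 + 11 × 2 = 33 if every hospital has one; this number is inferred. The protocol gives no job-loss rate. The 25% attrition mixes stopping work, long-term sick leave and non-return, so the range tried is 3% to 25%. No figure in the protocol can be reproduced for this point; the check is whether equal risks return an odds ratio of 1.

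**Step 1: one visit, therapist variance known.** On the logit scale, τ² = ICC/(1 − ICC) × π²/3 = 0.05/0.95 × 3.290 = 0.173. Solve E[expit(b + u)] = p for b, with u ~ N(0, τ²). The limiting odds ratio at equal risks is exp(b − logit p).

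- At p = 12%: logit p = −1.992 and b = −2.057, so OR = exp(−0.065) = 0.937.
- At 3%, 5%, 10%, 20% and 25%: OR = 0.922, 0.926, 0.934, 0.951 and 0.959. At 50% it is 1.00.
- ICC 0.10 at 12%: 0.875.
- If 0.05 is instead read as an ICC on the probability scale: 0.82 at 10% and 0.91 at 20%.

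**Step 2: one visit, variance estimated.** Simulated maximum-likelihood fits with no true difference, 120 per arm, 33 therapists and logit-scale ICC 0.05 gave geometric mean odds ratios of 0.85 (10% risk), 0.88 (12%) and 0.91 (20%). Medians were about 0.9. With true therapist variance zero the means were still 0.91 (10%) and 0.93 (20%), because a variance estimate cannot go below zero. Part of the one-visit shift is therefore small-sample estimation.

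**Step 3: both visits stacked.** Same settings, therapist intercept in WORKWELL only, no participant term, job loss persisting. Ranges are over repeated simulations.

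| Setting (no true difference) | Median OR at 12 months |
|---|---|
| 12% out of work at 12 months (6% at 6 months) | 0.59 to 0.64 |
| 20% out of work at 12 months | 0.72 to 0.78 |
| 12%, true therapist variance zero | 0.64 |
| 12%, 22 therapists | 0.70 |
| 12%, half of those out at 6 months return | 0.78 |
| Job loss independent between visits | 0.91 |
| Participant effect added in both arms (150 trials, bounded variance) | 0.71 |
| Ordinary logistic regression | 1.00 |
| Same mixed model, risks averaged over therapists | 1.01 |

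At 12%, 55% to 59% of null trials gave an odds ratio below 0.67, against 16% to 17% with ordinary logistic regression. The 0.64 at zero therapist variance shows that within-person persistence, loaded onto the therapist variance, drives most of the stacked shift.

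**Step 4: other coding of controls.** With controls as one-person clusters sharing the variance, both arms are conditional at a single visit and the shift should vanish. With stacked data it reverses: median about 1.4 in one set of 200 trials per setting and 1.8 in another of 300.

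**Step 5: tests.** At one visit, two-sided rejection under no difference was 2.7% to 4.1%. Stacked, false benefit and false harm were 2.5% and 0.3% at 12%, and 5.8% and 1.3% at 20% (2.5% nominal each; 400 trials, 108 per arm). Power to detect real harm in the stacked persistent model was 33% at 12% v 24% (ordinary logistic 64%) and 68% at 12% v 30% (ordinary 93%). At 12 months only, 12% v 24%, it was 53% against 65%.

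**The case against.** The protocol does not write a WORKWELL-only effect into the model. That is inferred from a sample-size assumption and a remark about blinding. Coding of controls and repeated-measures structure are ordinary content for the statistical analysis plan, which is not shown. This stands, and it limits the claim about size and direction. It does not rescue the Blinding sentence, which is a general statement and is wrong for the logistic and ordinal models that Statistical methods names.

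The analyses are first run without therapist effects, so an ordinary estimate will exist and a large move would be seen. That is a partial safeguard. But the protocol tells the reader that no such move can occur, and does not say which binary estimate to believe if it does.

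An effect for a typical therapist is a legitimate target. True, but then both arms should be on that footing. A coefficient conditional in one arm and marginal in the other is neither target.

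A reader might infer that the work-status odds ratio is bound to favour WORKWELL by a wide margin, that false claims of benefit become common, or that harm could not be detected. The documents and checks do not support this. The large figures need job-loss rates, persistence and the absence of a participant term, none of which the protocol states. Direction depends on how controls are coded. For an ordinal outcome, which work status may be, the shift changes sign between cut-points either side of 50%. Rejection rates are little affected apart from a modest excess in the stacked 20% setting. Harm stays detectable, with reduced power.

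**Conclusion.** The point holds in limited form. The statement that therapist adjustment affects only precision is right for the linear models and wrong for the mixed logistic and ordinal models to which the same method is carried over.

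On the natural reading, with the effect in WORKWELL only, the odds ratio for being out of work falls below 1 at equal risks. The shift is small at one visit: a limit of 0.93 to 0.95 at 10% to 20% risk and logit-scale ICC 0.05, and about 0.9 with the variance estimated at trial size. It can be large, with a median of about 0.6 to 0.8, if both visits are stacked with persistent job loss at assumed rates of 12% to 20% and no participant term.

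The harm is a misleading estimate for a secondary outcome and some loss of power to detect a worse result on WORKWELL. The WLQ-25 primary analysis and the other outcomes analysed by linear models are not affected.

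**What to change.** For binary and ordinal outcomes, make the reported contrast population-average in both arms, in one of two ways:

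- Logistic or ordinal regression with group, time, group-by-time, stratum and baseline, with cluster-robust standard errors (cluster = therapist in WORKWELL, participant in control) and a small-sample correction.
- If the mixed model is kept, average its predicted risks over the random effects before comparing arms, and do not report its raw group coefficient.

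Report a marginal odds ratio or a standardised risk difference at 12 months. Limit the Blinding sentence on precision to the linear models.

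The cost is a sentence or two in the plan and a few lines of code, with no new data. The drawback is that robust standard errors with about 33 therapist clusters (an inferred number) need the small-sample correction.
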